#### Secondary outcome parameters

##### Functional outome

As part of current clinical protocol, functional outcome will be measured using the Dutch version of the Hip disability and Osteoarthritis Outcome Score (HOOS), validated by De Groot et al [18]. Functional score will be recorded pre-operatively and at 6 weeks, 3 months and one year follow-up, as part of standard follow-up protocol [18]. Follow-up protocol is not affected by this study.

##### Position of the prosthesis

position of the prosthesis will be measured on AP-pelvis x-rays by two independend assessors blinded for the case number and level of experience.

##### Complication rate

complications: peri-operative and post-operative will be recorded by independent nurse practitioners blinded for the case number.

### Participating centres

The study will be a cooperation between the Academic Medical Centre Amsterdam, the Onze Lieve Vrouwe Gasthuis (OLVG) Amsterdam, The Isala Hospital Zwolle and McMaster University Hamilton, Canada. Surgical procedures will be performed by several surgeons at the OLVG Hospital in Amsterdam and the Isala Hospital in Zwolle. The learning of each individual surgeon will be analysed. Analysis will be performed at the Academic Medical Centre in Amsterdam by an independent assessment committee.

### Variables

#### Independent variable

Level of experience

We aim to compare 4 surgeons with different levels of experience in implanting non-cemented stems. Experience will be defined in years post board registration and number of arthroplasties performed per year.

#### Dependent variables

Four types of actions are analysed:

1. Goal Oriented Actions (GOA)

2. Repetitions

3. Additional Actions (AA)

4. waiting

#### Controlled variables

• Interval between operations

For valid comparison of the learning curve, time between procedures cannot exceed more than 1 month.

• Patient population

Inclusion criteria of patients

Adult patients with disabling degenerative arthritis of the hip or (avascular) head necrosis.

Maximum age is determined by the current clinical protocol of each participating hospital.

Exclusion criteria of patients

Patients not eligible for CFP arthroplasty in this study are:

Patients with a BMI of more than 40

Patients with skeletal immaturity

Patients with a life expectancy of less than 3 years

Patients with altered anatomy resulting in impossibility for the CFP procedure, according to the surgeon e.g.:

-hip dysplasia with high dislocation

-post traumatic severe anatomy change

Patients with extremity amputation

Patients with an active malignant disease or current cytostatic treatment

• Surgical technique

Predefined in the taxonomy

### Sample size

Since there is currently no data on the learning curve of the CFP stem, sample size is estimated by reviewing the learning curve of other implants or techniques in current literature. Previous literature on learning curves in total hip and total knee arthroplasty determine the learning curve on the amount of complications, clinical outcome, implant position or mean operative time [6,19].

Archibeck et al. analysed the first experience of 159 surgeons with the 2-incision minimally invasive THA. He found a significant reduction in the mean operative time in the first ten cases. The amount of complications did not show any reduction as a function of the case number [19].

Flamme et al. studied the learning curve in total hip arthroplasty of three surgeons with different levels of experience operating on a total of 168 patients. They found no association between functional outcome as determined by the Merle d'Aubigné score and case number. However considering intraoperative complication rate, all three surgeons ended their learning curve after a maximum of 20 cases [6]. Based on these studies, we estimate the efficiency to reach a plateau between 10 and 20 cases. Therefore the first 20 cases of each surgeon will be analysed.

A learning curve can however differ between individual surgeons. It is therefore important to study multiple surgeons with different levels of experience and to define a stopping rule. The stopping rule defines whether the estimated number of 20 cases is sufficient to study an individuals learning curve and terminate the task analysis or whether additional cases are needed. The criterion for terminating the task analysis was previously determined through the probability of failure (P) multiplied by the cost of failure (C) to an acceptable level – the P × C rule [20]. The role of the P × C rule is to save the analyst time in analysing tasks where the error variance would be inconsequential and to guide more exploration where the error variance would be intolerable [20]. The cost of failure is inherent to the clinical consequence of a peri-operative complication which requires clinical interpretation. We defined three major peri-operative complications during total hip arthroplasty which determined C:

1. massive bleeding

2. fracture (femoral or acetabular)

3. evident neurological damage

This resulted in the following definition of the stopping rule: if a surgeon encounters a major complication (C) within the last five consecutive surgical procedures (P), the stopping rule is considered unacceptable and an additional five surgical procedures have to be analysed.

To facilitate comparison of different levels of expertise we suggest one surgeon less than five years board certification, two surgeons 5 to 15 years and 1 surgeons more than 15 years board certification. This justifies our total sample of 4 surgeons each performing 20 cases, resulting in a total of between 80 surgical interventions to be analysed.

### Data acquisition

With the use of three cameras and a microphone, video-recordings are made of abovementioned procedures. One wide-angle (or fish eye) camera is positioned proximally 1,5 meters above the operating table, to record an overview-image of the operating theatre. A second camera is situated on the head of the surgeon to record a clear view of the actions performed by the surgeon. An additional portable camcorder is used to film any actions that are missed by the previously mentioned cameras. Sound is recorded with use of the camcorder. The total number of persons required to be present in the operating room during the operation is limited to only one.

A Quad unit combines four signals, 3 video and 1 sound, into one signal. This way, all images can be analysed simultaneously on one laptop on a split-screen (see Figure 1 and see Additional file 1: movie sample TAA).

**Figure 1 F1:**
[figure not shown]
Setup in the Operating Theater.

### Equipment

Theatre setup

• 3 camera's

◦ One camcorder camera on a stand

◦ One camera to be placed on the head of the surgeon

◦ One fish eye camera to be placed above the operating theatre

• Quad unit

• AV-converter

• Software for video analysis and image conversion

• Laptop with digital video portal.

### The Taxonomy

Time-action analysis is a quantitative method which can be used to objectively analyse the course of a surgical procedure. The analysis is done by scoring strictly defined actions in time. This way a procedure can be observed in detail and knowledge can be obtained about the difficulty and efficiency of a procedure and the comparison of two procedures can be performed objectively.

In performing a time-action analysis a taxonomy is used; a list of predefined Goal-Oriented Actions (GOA) which; taken together, describe the total procedure. The concept of time-action analysis described by Minekus [12] served as a template for the design of this taxonomy and has been modified for the CFP stem surgical technique. A GOA is defined as an action which contributes directly to the progress of the procedure [12]. The GOA's can then be divided in a number of Separate Actions (SA). For example, in the GOA *skin incision*, the SA's are: skin incision and positioning retractors. By formulating the GOA's as accurate as possible, almost every recorded action can be defined. This way of grouping separate actions into GOA's was chosen, since it would not have been feasible or efficient to separately score every action seen in a 90 minute film. Eventually the operative procedure is divided in Goal Oriented Phases (GOP);

1- Incision phase,

2- Prosthesis phase, subdivided in

a. femoral phase

b. acetabulum phase

c. stem phase

3- Closure phase.

These GOP's are divided in GOA's and at last, the GOA's are subdivided in SA's. All essential actions of the procedure are defined, e.g. sawing, cutting, suction, coagulating, placing of retractors. Extra sections are added for 'waiting' and 'additional actions' to be able to eventually account for every second of film.

Apart from formulating this list of pre-defined steps it is very important to come to good general agreements on the methods of scoring so that the inter-observer variation is limited to a minimum (see Table 1 in Additional file 2).

### Construction of the taxonomy

Using a method similar to Sarker et al. a template taxonomy is constructed using currently available literature on CFP stem surgical techniques [21,21]. The template taxonomy is discussed with participating surgeons and adjusted to represent individual surgical technique. This results in the final taxonomy, which is defined prior to analysis. During the course of the analysis the structure of the taxonomy is fixed.

### Task analysis

After scoring the video, a task analysis will be performed using the predefined taxonomy. This results in an hierarchical (studying procedural sequences) task analysis.

The duration and number of all actions are categorised in (Figure 2):

1. Goal Oriented Actions (GOA's)

2. Repetitions

3. Additional actions (AA's)

4. Waiting

GOA's are actions which contribute directly to the advancement of the procedure. Furthermore they are performed in consecutive order during each fase corresponding with the pre-defined taxonomy.

A GOA inadequately executed may require a Repetitions. Repetitions are Separate Actions (SA's), which are repeated due to insufficient progress of the procedure. An example of a Repetition is inadequate exposure, which causes insufficient progress and necessitates extending the incision, or repositioning the retractors.

A surgeon may encounter difficulties requiring actions not defined in the taxonomy. These actions are defined as AA's. This may be either due to abnormal anatomy, unexpected pathology, instrument failure or an inadequately executed goal-oriented action. Since we merely describe the External Mode of Malfunction, instead of the mechanisms or causes of malfunction we do not subcategorise additional actions by their cause. As Rassmussen put it: "For performance in unfamiliar situations requiring proper problem solving, a cognitive task analysis, if at all possible, requires interviews and discussions with the performer [22]." This results in a subjective analysis of an opinion. To obtain objective data additional actions will be categorised irrespective of their cause.

Waiting is the amount of time between two actions, with a minimum of 5 seconds.

While the amount and duration of GOA's is an expression of the level progress during the operation, delay is defined by the amount of time spend on Reptitions, AA's and waiting. The level of efficiency is an expression of the level of progress and delay.

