##### Data analysis

A regression analysis will be performed to reveal any significant increase of efficiency or decrease of the errors rate as a function of the case number.

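### The patient population is called controlled but is only bounded by eligibility, and the stated regression on case number includes no patient factor, so a change in case difficulty cannot be told from learning

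*Protocol article*

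**What the plan says.** Under Controlled variables, the article lists the patient population beside the interval between operations and the surgical technique. The control consists of eligibility criteria:

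- Degenerative arthritis and head necrosis are both eligible, and BMI is limited only at 40.
- On age: "Maximum age is determined by the current clinical protocol of each participating hospital".
- On anatomy, the exclusion reads "Patients with altered anatomy resulting in impossibility for the CFP procedure, according to the surgeon", followed by two examples and no threshold.

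Under Interventions, allocation of the stem is left outside the study's influence.

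Under Task analysis, the origin of additional actions is described as follows: "This may be either due to abnormal anatomy, unexpected pathology, instrument failure or an inadequately executed goal-oriented action". The section then declines to separate these causes: "To obtain objective data additional actions will be categorised irrespective of their cause". Under Primary outcome parameters, all additional actions enter delay, and efficiency is the share of the procedure that is nett Goal Oriented Action (GOA) time.

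Under Data analysis, the plan is one sentence, which makes case number the predictor: "A regression analysis will be performed to reveal any significant increase of efficiency or decrease of the errors rate as a function of the case". No patient characteristic is named there.

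**The concern.** Case number is the exposure of interest. Anything else that changes with it and also affects efficiency is confounded with learning. Patient difficulty is such a factor by the article's own account, because abnormal anatomy and unexpected pathology generate additional actions, and these lower efficiency however well the surgeon performs. Eligibility removes extreme patients but does not equalise difficulty among those who remain.

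Two research questions are exposed. The main one, the number of cases to proficiency, depends on the shape of each surgeon's curve over about 20 cases. The secondary one compares surgeons by experience, with one surgeon in the lowest band, two in the middle and one in the highest, spread over two hospitals whose age limits may differ. A difference in case mix between surgeons or hospitals would fall directly on that comparison.

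**Working it through.** **The plan's own figure.** 4 surgeons × 20 cases = 80 procedures, as stated under Sample size. No alpha, power, SD or effect size is given; the 20 cases rest on an expected plateau ("Based on these studies, we estimate the efficiency to reach a plateau between 10 and 20 cases"). There is therefore no power calculation to reproduce. Every size below rests on assumptions that are not in the documents.

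**Effect on one case.** Assume a 90-minute procedure (the film length mentioned under The Taxonomy) with 67.5 minutes of nett GOA time. Efficiency is 67.5/90 = 75%. Add anatomy-driven additional actions with surgical performance unchanged:

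- 5 minutes: 67.5/95 = 71.1%
- 10 minutes: 67.5/100 = 67.5%
- 15 minutes: 67.5/105 = 64.3%

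**Effect on the slope.** If patient-caused delay costs D points of efficiency, growing linearly from case 1 to case 20, the fitted linear slope changes by exactly D/19 points per case. Assume true learning of 15 points, rising linearly to a plateau at case 15. The least-squares slope without drift is 0.87 points per case.

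- D = 5: 0.87 − 5/19 = 0.87 − 0.26 = 0.61
- D = 10: 0.87 − 10/19 = 0.87 − 0.53 = 0.35 (before rounding, 0.874 − 0.526 = 0.348)

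**Effect on the plateau.** Same curve with residual SD 4 points; a broken line is fitted by least squares with the change point searched over cases 3 to 20. Median estimate over simulated surgeons:

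| True plateau | No drift | 5 points harder by case 20 | 10 points harder | 5 points easier |
|---|---|---|---|---|
| Case 15 | 15 | 14 | 12 | 16 |
| Case 12 | 12 | 11 | 9 to 10 | 13 |

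With no drift and a true plateau at case 15, the 5th to 95th percentiles of the estimate already run from case 10 to case 20.

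**Effect on the significance test.** A second simulation (20,000 runs per setting, baseline efficiency 75%) let the share of anatomically difficult cases drift linearly, with 5, 10 or 15 extra minutes per difficult case. The test was two-sided at 5% on one surgeon's slope.

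- No learning, constant share of 30%: about 2.5% false positives in each direction, as it should be.
- No learning, share falling from 50% to 10%: apparent gain of about 1.6, 3.0 or 4.2 points over 20 cases. A significant improvement appears in 7%, 11% or 14% of surgeons at SD 4, and in 4%, 7% or 8% at SD 8.
- No learning, share falling from 60% to 0%, 15 minutes: apparent gain of about 6.4 points, significant in 27% (SD 4) or 14% (SD 8).
- True learning of 10 points, 10 minutes, share rising from 10% to 50% instead of constant at 30%: the fitted gain falls from about 9.4 to 6.0 points. Detection falls from 57% to 28% (SD 4) or from 28% to 14% (SD 8).

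**Does the article already hold a remedy?** The abstract treats nett GOA time as representing difficulty. That measure subtracts delay, so anatomy-driven additional actions are not in it. It is also the numerator of efficiency and itself a primary outcome. It cannot serve as an independent adjuster for patient difficulty.

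**The case against.** The strongest reply is that a condensed article need not list covariates. The Data analysis sentence states a purpose and does not exclude adjustment, and an unseen analysis plan may include it. This stands in part: one cannot say that case number is the only predictor the investigators will ever use. But the article does more than leave a covariate unnamed. It declares the patient population controlled, which the criteria do not achieve, and the regression it does state leaves patient factors out.

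The second reply is that coding without cause is deliberate. Task analysis argues that assigning causes would require interviews and would turn the score into opinion. That reason is sound, and the coding should stay. A separate code for external causes would bring back the judgement that the article rejects, and instrument failure is in any case not patient difficulty.

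Three stronger readings are tempting and are not supported:

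- *That the operating surgeon sets eligibility.* BMI, skeletal immaturity, life expectancy, amputation and malignancy are fixed criteria, and the age limit is the hospital's. Only anatomical infeasibility is the surgeon's call. The Interventions section says the study does not influence stem allocation; it does not say who decides it.
- *That surgeons will take easier hips first.* Nothing in the documents shows this.
- *That a surgeon would be cleared for the later randomised trial too soon.* No clearance rule based on the efficiency plateau is stated. The only rule, under Sample size, concerns major complications and decides how many cases are analysed.

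It is also fair that a one-case shift is small beside a sampling range of cases 10 to 20.

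**Conclusion.** The point holds in a limited form. The population is restricted, not controlled; patient-caused delay lowers the primary outcome; and the stated regression has nothing to separate a trend in case difficulty from learning, or a difference in case mix from an effect of experience. This is a weakness in what the analysis can distinguish. It is not evidence that the results will be biased.

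The size depends wholly on assumed drift. A loss of 5 points by case 20 (a third of the assumed 15-point learning effect) moves the median plateau by about one case; 10 points moves it by two to three. Drift towards easier cases pushes the other way and can look like learning. Under mild drift the shift is minor relative to noise, but unlike noise it does not average out if surgeons drift in the same direction.

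**What to change.** 1. Keep the cause-blind coding of additional actions unchanged.
2. Add BMI, age and diagnosis (arthritis or head necrosis) to the regression under Data analysis. All three are already needed to check eligibility. Estimate their coefficients in common over all 80 cases, with each surgeon keeping a separate curve. With linear BMI and age and a two-level diagnosis, this spends 3 parameters on 80 cases instead of 3 on each surgeon's 20.
3. Report the adjusted and unadjusted curves side by side.
4. For each surgeon, show these covariates against case number, so that a reader can see whether case mix moved.
5. Under Controlled variables, describe the patient population as restricted by eligibility.

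The cost is analysis wording, a few degrees of freedom, and a somewhat wider interval for the case-number effect if a covariate does trend with it. No patient care changes. The remedy is partial, because these three variables capture anatomical difficulty only in part. If, by assumption, they explained half of a 5-point drift, the slope bias would fall from 5/19 = 0.26 to 2.5/19 = 0.13 points per case. The report should state that limit.

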### Femoral neck preserving hip arthroplasty

The Biodynamic cementless total hip prosthesis, introduced by Pipino in 1979, was designed with the aim to preserve maximum amount of bone stock for future revisions, to achieve physiological compression, tension and torsion forces and to minimise damage to vascular structures in the proximal femoral region [14,15]. The Biodynamic stem was replaced by the modified CFP prosthesis in 1996. The CFP prosthesis is made of titanium alloy with a hydroxyapatite porous coating, with longitudinal ribs to promote osseointegration. A seven year follow-up study of 353 CFP stem showed 99% good intergration, with only 2 cases of radiographically proven aseptic loosening [16]. It has a built in anatomic anteversion and 117° and 126° CCD angles to closely resemble physiological anatomy. Clinical follow-up showed good functional recovery and DEXA analysis of 10 patients showed minimal periprosthetic bone loss [14,16,17,17]. The CFP stem is combined with a Trabeculae Oriented Pattern (TOP) cementless hemispheric cup. The TOP cup has a biequatorial dissociation with a medialcaudal recess to allow a wider range of motion and a cranial rim reaching over 180° to reduce the risk of dislocation [14]. A clinical follow-up study of 301 TOP cups showed no detachement, migration, or osteolysis after 7 years [16].

Currently the CFP stem has not been compared with conventional straight stems in an RCT, therefore additional benefits remain to be determined. Implantation of the CFP stem requires a major alteration of operating technique compared to conventional straight cementless stems and require specially designed instruments. Therefore a substantial learning curve is to be expected potentially compromising the validity of an RCT due to differential expertise based bias. Determining the minimum number of cases required before participating in an RCT is often arbitrary and for many complex procedures the learning curve has not reached a plateau after reaching the required number of procedures [2]. Another potential for differential expertise bias is the influence of the number of years of clinical experience of participating surgeons [2].

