### Main objective/research question

What is the number of cases needed for surgeons with different levels of experience to reach proficiency with the CFP stem arthroplasty?

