### Hypothesis

We hypothesize that after 10–15 cases, surgeons will reach a plateau of the level of efficiency. We expect to register a significant decrease of errors during this period. Furthermore we expect no correlation to exist between change of functional outcome or complication rate and case number.

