## Methods

### Outcome

#### Primary outcome parameters

• Nett Goal Oriented Action Time = time spend on Goal Oriented Actions (GOAs) – delay

• Delay = time spend on repetitions, additional actions and waiting

• Efficiency = percentage of nett Goal Oriented Action Time during each procedure

• Level of difficulty = Nett Goal Oriented Action Time of a specific GOA + time spend on repeating that GOA during subsequent GOAs

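### Efficiency counts every unattributed wait of 5 seconds or more as delay, so its plateau can partly reflect the theatre team; report the learning curve with and without waiting

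*Protocol article*

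**What the plan says.** The main objective concerns the surgeon: "What is the number of cases needed for surgeons with different levels of experience to reach proficiency with the CFP stem arthroplasty". The hypothesis is framed on efficiency: "We hypothesize that after 10–15 cases, surgeons will reach a plateau of the level of efficiency". The abstract's discussion adds that the curves will serve to judge each surgeon's skill and to compare surgeons before the RCT.

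Under Primary outcome parameters the components are fixed: "Delay = time spend on repetitions, additional actions and waiting" and "Efficiency = percentage of nett Goal Oriented Action Time during each procedure". Under Task analysis, "Waiting is the amount of time between two actions, with a minimum of 5 seconds"; nothing there says whose waiting it is. The same section gives the possible origins of additional actions: "This may be either due to abnormal anatomy, unexpected pathology, instrument failure or an inadequately executed goal-oriented action". It then decides not to separate them: "To obtain objective data additional actions will be categorised irrespective of their cause".

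The controlled variables are the interval between operations, the patient population and the surgical technique. The Data analysis section regresses efficiency and error rate on case number and names no other term. The Background notes that "Implantation of the CFP stem requires a major alteration of operating technique compared to conventional straight cementless stems and require specially designed instruments".

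**The concern.** Efficiency is a share of the whole procedure, so anything that shortens waiting raises it, whoever was responsible for the wait. Instruments that are new to a surgeon may also be new to the staff who prepare and hand them over. If the staff become quicker as cases accumulate, waiting falls with case number, which is the regressor. Part of the measured curve would then belong to the team, and the estimated number of cases to proficiency could shift.

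The comparison between surgeons is exposed too. Four surgeons work at two centres, so at least one centre has two or more. If they share a team and start at different times, the later one would begin with trained staff and could look like a faster learner. The experience groups hold one, two and one surgeons, so such an effect would not average out.

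**Working it through.** **Figures in the protocol.** The planned total reproduces: 4 surgeons × 20 cases = 80 procedures. The Taxonomy section mentions a 90-minute film. The protocol gives no efficiency value, no split of procedure time and no case-to-case SD, so everything below on size is an assumption shown as a range.

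**Formula.** The Taxonomy section wants every second of film accounted for, so I read the definition as

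efficiency = nett GOA / (nett GOA + repetitions + additional actions + waiting).

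The waiting-free version is nett GOA / (nett GOA + repetitions + additional actions).

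**Waiting falls, surgeon unchanged.** Assume a first case of 90 minutes with repetitions 8 and additional actions 7. Nett GOA time is the remainder and stays constant.

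| Waiting, min | Nett GOA, min | Efficiency, start | Efficiency, end | Change, points | Waiting-free, both times |
|---|---|---|---|---|---|
| 5 to 3 | 70 | 70/90 = 77.8% | 70/88 = 79.5% | 1.8 | 70/85 = 82.4% |
| 10 to 5 | 65 | 65/90 = 72.2% | 65/85 = 76.5% | 4.2 | 65/80 = 81.3% |
| 15 to 5 | 60 | 60/90 = 66.7% | 60/80 = 75.0% | 8.3 | 60/75 = 80.0% |

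**Would the planned regression pick it up?** A surgeon who does not learn was simulated over 20 cases, 4000 runs per setting. Waiting declined exponentially towards its end value (time constant 5 cases), with normal case-to-case variation and a linear fit at two-sided 0.05 (assumed). The chance of a significant positive slope was:

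| Waiting, min | SD 3 points | SD 5 points | SD 8 points |
|---|---|---|---|
| constant at 10 | 2% | 2.5% | 3% |
| 5 to 3 | 9% | 6% | 4% |
| 10 to 5 | 31% | 14% | 9% |
| 15 to 5 | 84% | 43% | 20% |

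This concerns the slope. The shift in the plateau case number was not simulated.

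**Additional actions.** Hold waiting at 10, repetitions at 8 and nett GOA at 65 minutes. If additional actions fall from 7 to 3 minutes because cases get easier, efficiency goes from 65/90 = 72.2% to 65/86 = 75.6%. If they rise from 3 to 7 minutes, it falls by the same amount. The waiting-free measure moves as well, from 65/80 = 81.3% to 65/76 = 85.5%. Leaving out waiting therefore does not deal with case mix.

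**The case against.** Several points on the other side stand.

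- **Team learning is an inference.** The protocol does not say that waiting includes instrument handling by staff, that the team is new to the stem, that surgeons share a team or that they start at different times. The Study design section describes surgeons with differing experience of this stem, so a team may already know it. A reader might infer that team learning will appear as surgeon learning; the text supports only that it can.
- **Pooling causes of additional actions is deliberate.** Task analysis argues that assigning causes would need interviews and would be subjective. That is a reasoned choice. The argument is made for additional actions, however, and waiting can be set apart without judging any cause.
- **Repetitions are not the one surgeon-specific component.** A reader might draw that contrast, but the protocol ties repetitions to insufficient progress of the procedure and lists poor execution among the causes of additional actions.
- **Case mix is partly controlled by eligibility.** It distorts a surgeon's own slope only if it drifts with case number, and then in either direction. Otherwise it adds noise, or confounds the comparison if it differs between surgeons.
- **Other primary parameters contain no waiting.** Nett GOA time and level of difficulty are examples. The plateau hypothesis, though, is stated on efficiency.
- **Waiting may include the surgeon's own hesitation**, which is plausibly part of learning. This argues against replacing the defined measure.

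Component curves could also be planned in a document not shown. The definition of efficiency and its reading as surgeon proficiency are fixed in this one.

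**Conclusion.** The point holds as a limit on interpretation with a cheap remedy. By definition efficiency includes unattributed waiting; its plateau is read as the surgeon's proficiency; and neither the controlled variables nor the stated regression takes account of the theatre team. If waiting falls for reasons outside the surgeon, efficiency rises by about 2 to 8 points under the assumed splits. The resulting chance of a spurious significant slope runs from near its nominal 2.5% (4% at the mildest fall and SD 8) to 84% (the largest fall and SD 3). All minute values and SDs are assumptions, so these figures show that the effect can matter and not that it does.

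The documents do not support a stronger conclusion that the measure is invalid, that it should be replaced, or that team learning and case mix necessarily produce the curve.

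**What to change.** Keep the all-inclusive efficiency as defined. For each surgeon, fit two further series against case number: nett GOA / (nett GOA + repetitions + additional actions), and waiting time itself. Report the plateau case number and the comparison between surgeons with and without waiting. Attribute the plateau to the surgeon only where the two agree, and state beforehand how close the two case numbers must be to count as agreement. Where they differ, show the waiting curve and describe the result as that of surgeon and theatre together.

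No new recording or rescoring is needed, because the number and duration of the four action types are already recorded separately. The cost is two more curves per surgeon. The waiting-free measure leaves out the surgeon's hesitation and so only supplements the defined one. Neither measure separates the causes of additional actions, and the report should say so, together with the caveat on case mix.
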